## Abstract

**Background:**

Pressure ulcers are one of the most common health complaints, which often take months or years to heal, and affect patients’ morbidity and quality of life. Medical options for pressure ulcers are limited. Electroacupuncture (EA) has been employed to relieve the symptoms for patients with pressure ulcers, but there is limited clinical evidence for its effectiveness.

**Methods/Design:**

This study consists of a randomized controlled trial (RCT) with two parallel arms: a control group and an EA group. Both groups will receive standard wound care (including changing position, using mattresses and cushions, and a good diet) of five sessions per week for a total of 40 sessions during the 8-week treatment period. In addition, the EA group will receive the EA intervention. The following outcome measurements will be used in examination of participants: wound surface area (WSA), visual analogue scale (VAS), and the proportion of ulcers healed within trial period (PUHTP). All the outcomes will be evaluated at the start of the study, at the end of the fourth week, at 8 weeks after randomization, and 1 month after treatment cessation.

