**Safety**					
Adverse events		**×**	**×**	**×**	**×**

EA, electroacupuncture; PUHTP, proportion of ulcers healed within trial period; VAS, visual analogue scale; WSA, wound surface area; the symbol ‘x’ is used as a check mark.

This trial will include an 8-week treatment period and a 1-month follow-up period. After randomization, patients will receive a total of 40 session treatments over a period of 8 weeks. Outcome measurements will be assessed at baseline (1 week after participants are diagnosed with pressure ulcer), as well as at the end of the fourth week and 8 weeks after randomization, and 1 month after conclusion of the treatment phase. Patients will be informed that they may be assigned to an EA group, or control group.

This trial will be carried out according to the principles of the Declaration of Helsinki (version Seoul, 2008). This study protocol has been approved by the ethical review boards of the Second Affiliated Hospital of Heilongjiang University of Chinese Medicine, with permission number LLP2011012. All participants will be asked to provide written informed consent before enrollment, and will be given sufficient time to reach a decision to participate and sign the consent form.

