### Outcome measures

#### Primary outcome

1) Wound surface area (WSA)

The pressure ulcer surface area will be measured by the use of acetate tracing and subsequent planimetric determination. Ulcer tracings will be accomplished by outlining the pressure ulcer circumference onto a transparent film applied directly over the wound. Each ulcer will be traced three times by two assessors, respectively, in order to improve the accuracy of the tracings. The ulcer surface area will be determined from the wound tracing using a planimeter (KP-21C) by a third assessor. All three assessors will be blinded as to the identity of the patient and to the treatment group assignment.

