### Statistical methods

#### Sample size

This study is a pilot study for the evaluation of the efficacy of EA for patients with pressure ulcers and the feasibility of a large clinical trial. Because of the short duration, lasting 8 weeks, the desired sample size for this pilot study is 36 participants, with 18 participants in each group, assuming a dropout rate of 20%, which is the minimum sample size necessary to evaluate the effect of EA [21].

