#### Analysis

Data will be analyzed by a statistician blinded to the allocation of groups. Statistical analyses will be conducted using the SPSS 17.0 statistical software packages (IBM, Armonk, NY, USA), and the levels of significance will be reported at *P* <0.05. The intention-to-treat (ITT) population will be defined as the participants who are randomized and received at least one treatment session. The data analysis of baseline characteristics, as well as the primary and secondary outcomes will be based on the ITT principle. Analysis of covariance will be conducted unless the adjustment for possible baseline incomparability is needed.

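### No visit is named primary for wound surface area, so the plan does not exclude resting its efficacy conclusion on whichever of three visits is favourable

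*Protocol article*

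**What the plan says.** Under Primary outcome, the article lists a single item, "Wound surface area (WSA"), and then explains the technique: "The pressure ulcer surface area will be measured by the use of acetate tracing and subsequent planimetric determination". It specifies the tracings, the assessors, the planimeter and the blinding. It gives no time point and does not say whether the quantity compared is the area at a visit, the change or the percentage change.

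The schedule appears three times and is consistent. The abstract states "All the outcomes will be evaluated at the start of the study, at the end of the fourth week, at 8 weeks after randomization", and the sentence goes on to the follow-up visit. Table 1 marks WSA at weeks 0, 4 and 8 and at one month after the treatment phase. The text under Table 1 gives the post-baseline times as "as well as at the end of the fourth week and 8 weeks after randomization, and 1 month after conclusion of the treatment phase". No visit is singled out in any of the three places.

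Under Analysis, one statement covers primary and secondary outcomes alike: "the levels of significance will be reported at *P* <0.05". The only method named is in the sentence "Analysis of covariance will be conducted unless the adjustment for possible baseline incomparability is needed". No repeated-measures model, joint test, testing order or multiplicity rule is mentioned.

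The Sample size section calls the trial a pilot and refers to its 8-week duration, but does not make week 8 the primary time point. The Objective section makes efficacy the primary aim, and the Discussion expects the results to settle whether electroacupuncture works.

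**The concern.** A primary outcome defined only by its instrument is not yet a comparison. The three visits answer different questions: response midway through treatment, effect at the end of treatment, and whether an effect lasts after treatment stops. If they disagree, nothing in the article says which one decides the efficacy objective.

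What is at stake is how a positive result can be read. A significant difference at one visit could be presented as the primary finding, and a reader could not tell from this document whether that visit was chosen beforehand. The printed covariance sentence adds a further choice. As worded, it applies the method except where baseline adjustment is needed, so whether the primary comparison is adjusted for baseline WSA is also unsettled.

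**Working it through.** **Plan's own figure.** The article states no familywise error rate, so there is none to reproduce. Its only error-rate figure is the 0.05 level under Analysis. The sample size cannot be re-derived either, because no effect size, standard deviation or power is given. It serves here only to set realistic arm sizes: 18 per group with 20% dropout leaves 18 × 0.8 = 14.4, so 14 to 18 analysed per arm.

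**Inputs from the article.** One primary outcome; three post-baseline visits (week 4, week 8, one month after treatment); level 0.05; 1:1 allocation.

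**Assumptions not in the article.**
- Tests are two-sided.
- WSA is tested separately at each visit.
- A significant result at any visit counts as success.
- The test statistics at the three visits have correlation r, varied from 0 to 0.95. This r belongs to the test statistics. After adjustment for baseline it would usually be lower than the raw correlation between wound areas.

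**Independent case.** 1 − (1 − 0.05)³ = 1 − 0.857375 = 0.1426, or 14.3%.

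**Correlated case.** P(at least one |Z| > 1.96) for three standard normal statistics under no treatment effect, from 1,000,000 simulated draws per setting:

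| Assumed r | Equal correlation between visits | Correlation decaying with distance, AR(1) |
|---|---|---|
| 0 | 14.3% | 14.3% |
| 0.3 | 13.6% | 13.8% |
| 0.5 | 12.6% | 13.0% |
| 0.6 | 11.8% | 12.3% |
| 0.7 | 10.9% | 11.4% |
| 0.8 | 9.8% | 10.3% |
| 0.9 | 8.4% | 8.8% |
| 0.95 | 7.4% | 7.7% |

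The r = 0 row is the exact value.

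**Small-sample check.** Two-sample t-tests with 14 and 18 per arm give 12.5–12.7% at r = 0.5, 11.0–11.2% at 0.7 and 8.5–8.6% at 0.9. The normal approximation is adequate at this trial's size.

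**Range.** 7.4/5 = 1.5 and 14.3/5 = 2.9, so 1.5 to 2.9 times nominal. Counting only results that favour electroacupuncture, the rate is 3.7% to 7.3% against 2.5%, which is the same ratio.

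**Under a fixed rule.** One visit named in advance, or one joint test, at 0.05 gives 5%. Testing all three visits at 0.05/3 = 0.0167 holds the rate at or below 5% (simulated: 4.9% at r = 0, 3.9% at 0.7, 3.0% at 0.9).

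**The case against.** The strongest reply is that an assessment schedule is not a testing plan. The abstract, Table 1 and the text beneath it say when data are collected, and the same grid applies to every outcome. Nothing says that each visit will be tested or that any significant visit counts as success. This stands. A reader might infer that following the plan literally produces three tests of the primary outcome and so roughly doubles the false-positive rate. The documents do not support that: one visit chosen beforehand, or one joint test, fits the text equally well and keeps 5%. What can be said is that the text does not exclude visit-by-visit testing. Covariance analysis in its ordinary form takes one post-baseline value per fit, so separate tests are a natural reading but not the only one.

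A second reply is that a condensed article leaves such matters to a full protocol or analysis plan. This stands for multiplicity details and the handling of secondary visits. It is weaker for the primary time point, which is part of the endpoint's definition. The article's own primary-outcome section goes as far as the planimeter model without giving it.

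A third is that this is a pilot of 36 participants, where strict error control is not the main concern. That lowers the weight of the point. It does not remove it, because the Objective and Discussion attach an efficacy conclusion to the results.

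Finally, Table 1 separates treatment from follow-up, so the visits are not presented as interchangeable. True, but weeks 4 and 8 both lie in the treatment phase, and the separation ranks nothing.

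**Conclusion.** The point holds as a gap in the definition of the primary endpoint. WSA has three post-baseline visits, none is primary, and one 0.05 level covers everything, so the efficacy conclusion could be based on whichever visit is favourable. That much rests on the text alone and does not depend on any correlation.

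The size is conditional. If each visit were tested separately at two-sided 5% and any significant one counted, the false-positive rate would be about 7–14% instead of 5%. A figure of about 10%, double the nominal level, needs a between-visit correlation of about 0.7–0.8. That value may be plausible, but it comes from no part of the article, so it should not be reported as this trial's error rate. The calculation covers WSA only. It does not count the pain score, the healed proportion or the open choice about baseline adjustment.

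This should be corrected. The pilot status moderates its importance, and the remedy is nearly free.

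**What to change.** Add one statement to the primary outcome or Analysis section, settled before the statistician is unblinded and without sight of outcomes by group:

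- Name one primary time point for WSA. Eight weeks after randomisation, the end of treatment, is one candidate; the sponsor may justify another.
- Compare the groups on WSA at that visit by analysis of covariance always adjusted for baseline WSA, at two-sided 5%. This also replaces the conditional wording of the present covariance sentence.
- Report WSA at the other two visits, the pain score and the proportion of ulcers healed as secondary, with 95% confidence intervals and no confirmatory claim.

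If the sponsor wants all three visits to carry the primary claim, a joint test or a level of 0.0167 at each visit would serve instead.

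The cost is a sentence or two. The visits, the data collected and the sample size do not change. The one drawback is that a difference significant only at a visit other than the named one could not be claimed as the primary finding.

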**Discussion:**

The aim of this study is to evaluate the effectiveness of EA for the treatment of patients with pressure ulcers.

**Trial registration:**

Chinese Clinical Trial Register: ChiCTR-TRC-11001693

## Background

Pressure ulcers, also known as bedsores or pressure sores, are regions of localized damage to the skin and deeper tissue layers affecting muscle, tendon, and bone [1-3]. These pressure ulcers are caused by unrelieved pressure or pressure in combination with shear and usually over bony prominences, such as the sacrum (tailbone), back, buttocks, heels, back of the head, and elbows [4,5]. Open ulcers can become a source of pain, disability, and infection unless they are adequately treated.

The prevalence and incidence of pressure ulcers differ according to the method of data collection and classification. For example, this type of ulcer is widespread, with prevalence rates varying from 8.8% to 53.2% [6,7] and incidence rates fluctuating from 7% to 71.6% [8,9]. Prevalence rates vary widely depending on patients’ predisposing risk factors, such as poor nutrition, confinement to a bed or wheelchair, and so on [5,10,11]. Pressure ulcers are generally graded I, II, III, and IV, according to the European Pressure Ulcer Advisory Panel and the National Pressure Ulcer Advisory Panel (EPUAP/NPUAP) [12].

Intervention strategies for pressure ulcers often represent a great financial burden on healthcare systems. For example, the annual cost associated with treatment of pressure ulcers has been estimated to range from £1.4 to 2.1 billion in the UK; broadly equal to the total cost of community health services [1,13].

Effective and adequate intervention is an important issue for patients, practitioners, and policy makers. Herbal medicine, acupuncture, and moxibustion are three effective traditional Chinese medicine (TCM) therapies and have been administered for treatment of pressure ulcers in China [1]. However, the current level of evidence is poor because of small sample size, poor quality, rare follow-up, and variation in the composition of acupuncture. Considering these methodological flaws, we will conduct a trial to assess the efficacy of electroacupuncture (EA) for pressure ulcers and the feasibility of a large clinical trial.

## Methods/Design

### Objective

The primary objective of this study is to evaluate the efficacy of EA treatment for pressure ulcers.

### Design

This study will consist of a randomized, assessor- and analyst-blinded, controlled trial to compare an EA group with a control group (Figure 1 and Table 1). The trial will be conducted at the Second Affiliated Hospital of Heilongjiang University of Chinese Medicine, Heilongjiang Province, China.

**Figure 1 F1:**
[figure not shown]
Trial flow chart.

**Table 1 T1:** Visit times and data collection

**Data collection**	**-1 week**	**0 week**	**4 weeks**	**8 weeks**	**1 month after treatment phase**
	**Baseline**	**Treatment phase**			**Follow-up phase**
**Patients**					
Informed consent	**×**				
Sign the informed consent		**×**			
Medical history	**×**				
Physical examination	**×**				
Randomization		**×**			
**Intervention**					
EA group (n = 18)		40 sessions of EA; plus standard wound care			
**Comparison**					
Control group (n = 18)		40 sessions of standard wound care			
**Outcomes**					
WSA		**×**	**×**	**×**	**×**
VAS		**×**	**×**	**×**	**×**
PUHTP		**×**	**×**	**×**	**×**
**Safety**					
Adverse events		**×**	**×**	**×**	**×**

EA, electroacupuncture; PUHTP, proportion of ulcers healed within trial period; VAS, visual analogue scale; WSA, wound surface area; the symbol ‘x’ is used as a check mark.

This trial will include an 8-week treatment period and a 1-month follow-up period. After randomization, patients will receive a total of 40 session treatments over a period of 8 weeks. Outcome measurements will be assessed at baseline (1 week after participants are diagnosed with pressure ulcer), as well as at the end of the fourth week and 8 weeks after randomization, and 1 month after conclusion of the treatment phase. Patients will be informed that they may be assigned to an EA group, or control group.

This trial will be carried out according to the principles of the Declaration of Helsinki (version Seoul, 2008). This study protocol has been approved by the ethical review boards of the Second Affiliated Hospital of Heilongjiang University of Chinese Medicine, with permission number LLP2011012. All participants will be asked to provide written informed consent before enrollment, and will be given sufficient time to reach a decision to participate and sign the consent form.

### Randomization

A randomization scheme will be performed at the Good Clinical Practice (GCP) Center of the Second Affiliated Hospital of Heilongjiang University of Chinese Medicine. This scheme will be used to assign participants to the EA group and control group in a 1:1 ratio. The randomization scheme will be generated by the central computer system. Two separate databases will be set up: the ‘participants’ database that includes basic participant information, such as name, contact details, and so on; and the ‘randomization’ database that holds data of patients registered on the trial and their allocation [14]. The practitioners participating in the study will not take part in the randomization process. Patients who meet the inclusion criteria and agree to provide written informed consent will be included in the study. The researcher will then contact the GCP center where the participant’s information is registered, and the randomization information of the patient’s assignation to one of the two study branches will be sent to the researcher by cell phone or via email. This procedure will ensure adequate randomization concealment, and is not influenced by the researcher taking part in this study.

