### Eligibility

#### Inclusion criteria

Participants will be included if they fulfill the following criteria: 1) pressure ulcers of grade II or III, according to EPUAP/NPUAP [12]; 2) duration of one or more pressure ulcers is greater than 3 months; and 3) aged 18 to 75 years old.

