### Control group

Standard wound care will be used in the control group. In this study, standard wound care will include moving around and changing position, using mattresses and cushions, and a good diet. Keeping moving by moving around and changing position as much as possible should be restricted to less than 2 hours. Using mattresses and cushions can reduce the pressure on bony parts of the body. For patients with pressure ulcers of grade II, they should use a high specification foam mattress. As for pressure ulcers of grade III, patients should receive a more sophisticated mattress or overlay. A good diet of eating well and drinking enough water is very important. The healthcare professional will offer good dietary advice according to what is patients missing from the diet, their general health, and preferences.

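### Grade II and III ulcers are mixed at entry, but the stated analysis has no grade term and, as worded, drops ANCOVA when baseline adjustment is needed; adjustment for grade should be prespecified

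*Protocol article*

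**What the plan says.** The Inclusion criteria of the Protocol article admit "pressure ulcers of grade II or III, according to EPUAP/NPUAP". They also allow a patient to have more than one ulcer.

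The Control group section ties the support surface to grade. Grade II patients use a high-specification foam mattress, and for the others, "As for pressure ulcers of grade III, patients should receive a more sophisticated mattress or overlay". The Treatment group section adds electroacupuncture (EA) to the same standard care, so the rule applies in both arms.

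On allocation, the Randomization section says "The randomization scheme will be generated by the central computer system" and "This scheme will be used to assign participants to the EA group and control group in a 1:1 ratio". It describes the databases, the registration step and how the assignment is sent. It names no stratification, minimisation or blocking factor.

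The Sample size section says "the desired sample size for this pilot study is 36 participants, with 18 participants in each group, assuming a dropout rate of 20" (per cent).

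The Analysis section contains the only safeguard against baseline differences. It makes ANCOVA the method except where possible baseline non-comparability calls for adjustment, and it does not name ulcer grade as a covariate.

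**The concern.** Grade describes severity at entry and also fixes part of the background care. If one arm happens to receive more grade III patients, the unadjusted comparison of wound surface area (WSA) and of the proportion of ulcers healed (PUHTP) carries the whole grade effect: prognosis and the support surface together. In a trial of 36 such a gap is not rare.

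A covariate model would normally deal with this. The sentence that should provide it runs the wrong way round: read literally, it uses ANCOVA when baseline adjustment is not needed and drops it when it is. Even if the intended sense is the reverse, adjustment would depend on the imbalance observed, and grade would still not be named.

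The article makes efficacy its primary objective, tests at P < 0.05, and says in its Discussion that the results will settle whether EA is effective. Precision and comparability therefore matter even though the trial is called a pilot.

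**Working it through.** **Inputs from the article.** 36 patients, 18 per arm, 20% dropout; 1:1 allocation with no balancing factor described; grades II and III; significance at 0.05 (two-sided assumed).

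**Inputs not in the article, so assumed.** The share of grade III patients, and the effect of grade on WSA and on healing.

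**The plan's own figure.** No effect size, SD, healing rate or power is given, so 36 cannot be derived. Only the dropout step can be checked: 14 / (1 − 0.20) = 17.5, rounded up to 18 per arm. The figure is consistent with about 14 completers per arm.

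**1. Chance of a grade gap, binomial.** Let X and Y be the grade III counts in the two arms, independent Binomial(18, p).

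| Gap in grade III patients | p = 0.5 | p = 0.3 |
|---|---|---|
| at least 4 (4/18 = 22 points) | 0.243 | 0.201 |
| at least 5 (5/18 = 28 points) | 0.132 | 0.100 |

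**2. The same with exactly 18 per arm.** If K of the 36 are grade III, the count in one arm is hypergeometric(36, K, 18), and the gap is |2X − K|.

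| K | P(gap ≥ 4) |
|---|---|
| 9 | 0.12 |
| 12 or 24 | 0.29 |
| 13 | 0.16 |
| 17 or 19 | 0.18 |
| 18 | 0.32 |

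The values jump because the gap has the same parity as K. With odd K, a gap of at least 4 means at least 5. The range over these mixes is 0.12 to 0.32.

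**3. What a gap does to the unadjusted estimate.** Shift = grade effect × gap in proportions.

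- WSA, grade effect 0.5 to 1 SD, gap 4/18 to 6/18: from 0.5 × 0.222 = 0.11 SD to 1 × 0.333 = 0.33 SD.
- PUHTP, healing 25 to 40 points lower in grade III: from 25 × 0.222 = 5.6 points to 40 × 0.333 = 13.3 points.

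For scale, the difference detectable with 80% power is (1.96 + 0.84) × √(2/n): 0.93 SD at n = 18 and 1.06 SD at n = 14.

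**4. Operating characteristics.** Simulation of 8,000 trials per setting: 36 patients with no dropout, 18 of each grade, grade effect 1 SD, treatment effect 0 or 1 SD, two-sided 5% test.

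| Allocation and analysis | Type I error, all trials | Type I error when gap ≥ 4 | Power, 1 SD effect |
|---|---|---|---|
| Unstratified, unadjusted | 0.054 | 0.092 | 0.74 |
| Unstratified, grade-adjusted | 0.046 | 0.049 | 0.82 |
| Stratified, grade-adjusted | 0.049 | no such gap | 0.82 |

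The overall error rates are nominal within simulation error (standard error about √(0.05 × 0.95 / 8000) = 0.0024). Adjustment recovers the power and restores the conditional error rate. Stratifying the list as well adds almost nothing to either.

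The simulated model contains no baseline WSA. Where baseline WSA is also in the model and already carries part of the grade effect, the further gain from the grade term would be smaller than 0.74 to 0.82.

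**The case against.** The strongest objection is that this is silence in a condensed article. The Randomization section nowhere says that the list is simple or unstratified, and stratification factors and covariate lists are often left to a full protocol or SAP. That stands as far as allocation goes: a reader might infer that the list ignores grade, but the article does not establish it. It does not dispose of the analysis sentence, which is printed and defective as worded.

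Second, a reader might conclude that a sizeable imbalance is likely and that a treatment difference could then not be attributed to EA. The figures do not support this. A probability of 20 to 24% leaves 76 to 80% of allocations without such a gap. Randomisation already allows for chance imbalance, and overall type I error stays nominal. Even among trials with a gap of 4 or more, under a large assumed grade effect, it reaches only about 0.09.

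Third, the support surface might be read as a second confounder on top of severity. It follows grade by the same rule in both arms, so it is part of the grade effect and a grade term absorbs it. The article does not say whether it would add to or offset the difference in prognosis.

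Fourth, baseline WSA is measured at week 0 and could serve as a covariate. True, and it should be used; but it is not the same as grade, and the present wording does not secure its use either.

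**Conclusion.** The concern holds as a matter of precision and of distortion in the realised sample. It is not a bias in expectation and not a failure of randomisation. Under an assumed 30 to 50% grade III, a gap of at least 22 points has about a 20 to 24% chance (12 to 32% with exact 18/18 arms over mixes from 9 to 24 grade III of 36). Such gaps, up to 33 points, would move the unadjusted WSA difference by about 0.11 to 0.33 SD if grade is worth 0.5 to 1 SD, and PUHTP by about 6 to 13 points if healing differs by 25 to 40 points between grades. Omitting grade costs about 8 points of power (0.82 − 0.74) in the simulated case. The article gives neither the grade mix nor the effect of grade, so these are ranges under assumptions, and all would shrink if grade matters less. The improvement is cheap and worth making. No view is taken on the choice of support surface.

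**What to change.** Replace the conditional ANCOVA sentence in the Analysis section with a rule that does not depend on the imbalance observed:

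- WSA is analysed by ANCOVA with treatment, baseline WSA and ulcer grade at entry (II versus III) as terms.
- PUHTP is compared with adjustment for, or stratification by, grade; with this few patients a Mantel–Haenszel comparison over the two grades is the simpler choice.
- For a patient with several ulcers, grade is the highest eligible grade at entry, fixed before allocation.

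The cost is one degree of freedom and no new data, since grade is established at eligibility. The change should be dated and made before anyone sees outcomes by arm.

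Stratifying the central list by grade is optional, and only if the list can still be changed. The article says that recruitment is under way, and the simulation shows almost no gain beyond adjustment. If the full protocol already stratifies by grade, the article should say so, and the grade term belongs in the analysis all the same.
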